Participatory design sessions using design thinking and process improvement methods were conducted with clinicians, including physicians, residents, and nurses. The participating clinicians generally preferred to be alerted only when patients were identified by the model as *high risk* rather than see the model prediction for every patient. Therefore, we designed the system to only flag patients whose CDI score was higher than 65, which, based on our validation, was the optimal cutoff to identify patients at the highest risk for unplanned ICU transfers and RRT events. As the area under the curve was only 0.70, the discriminatory ability of the model was not sufficiently robust to warrant showing the individual integer score values (ie, we did not want users to mistakenly interpret a higher integer score within the high-risk group as translating into higher risk) [2,4]. Rather, we incorporated a population-level description of patients in the high-risk group with the statement that the flagged patients have a *1 in 5 chance of requiring a RRT or ICU transfer within the next 6-18 hours,* which is derived from our validation.

Three preferred alerting mechanisms for a patient identified by the model as high risk were identified: alert mode 1: a noninterruptive flag icon that appears on the screen next to patients classified as high risk in the EHR patient list view, which allows clinicians to quickly see the names of all patients classified as high risk on one screen; alert mode 2: a banner visible on top of the screen once the chart of a flagged patient is opened that provides additional information about what *high risk* means, the accuracy of the CDI model, and specific next steps that should be taken to assess the risk of deterioration; and alert mode 3: an interruptive alert delivered to mobile devices that includes the same information as the banner at the time a patient first crosses the high-risk CDI threshold.

Downstream workflows were designed to accompany these alert modes to improve the reliability and degree of team coordination in the clinical response for patients at risk of deterioration (Figure 1). Once the clinician receives the alert, they first assess the patient to judge whether the alert is clinically relevant and accurate and then conduct a huddle with the rest of the clinical team and use the following checklist to assess the patient’s risk and review mitigation strategies:

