Align on the anticipated reason for patient deterioration.Assess vital signs, airway or oxygenation needs, intravenous access, and code status.Agree on changes to care management (eg, aspiration precautions in place, critical care consultation, etc).Agree on the steps to take if the patient continues to deteriorate.

The last step involves documentation using an EHR-based documentation tool that captures the actions to be taken and the decisions made during this risk-of-deterioration huddle.

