### Implementation Strategy

The intervention implementation will be split into two stages to assess its impact when offered to the physicians only (stage 1) and later to the entire physician-nurse team (stage 2). In stage 1 (yellow shading in Figure 2), the three alert modes will be delivered only to the physicians for patients across all 6 patient care units, and subsequent workflows will be initiated only by the physician.

In stage 2 (green shading in Figure 2), the alert modes will also be delivered to the nurses on the clinical teams, and either the physician or the nurse on the team can initiate the downstream workflow, thus creating a team approach to identifying and managing clinical deterioration. Nurses are to perform a parallel clinical validation of the alert and contact the physician to conduct the aforementioned risk-of-deterioration huddle. Thus, assessment of the risk and initial steps to manage deterioration can be initiated by either the physician or the nurses in the team intervention model. Stage 2 will be rolled out in a stepwise manner to each of the 6 primary general medicine units.

Rolling out the intervention using a stepwise approach was chosen for pragmatic implementation and evaluation purposes. The physicians care for patients across all 6 patient care units, whereas the nurses are staffed based on individual units. For implementation practicality and patient safety, stage 1 (physician-only intervention) would thus be implemented across all 6 units, whereas the implementation of stage 2 (the addition of nurses) would be staggered by the patient care unit so that the nurses in each unit can be trained in the new workflow together. This implementation strategy also allows us to evaluate the additive impact of delivering AI predictions to the entire physician-nurse team using a stepped wedge design.

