### Sample

To evaluate this multidisciplinary intervention, data derived from multiple stakeholders, including providers, staff, and adult patients, will be included. The intervention will be implemented by providers and clinical staff in the 6 medicine units for all adult patients, as outlined in Figure 2. The clinical and process outcomes derived from the EHR and chart reviews will be captured at either the patient or unit level. The following patient inclusion criteria are based on the level of analysis:

For unit-level outcomes, all patients admitted to the units will be included in the analyses.For patient-level outcomes, patients who cross the high-risk CDI threshold (CDI≥65) during their inpatient stay and will thus be eligible for the intervention will be included in the analyses.

For the qualitative evaluation, a stratified purposeful sample of approximately 20 providers and clinical staff who are typically responsible for identifying deterioration in patients will be selected for interviews (eg, hospital residents or interns, bedside nurses, critical care response team, clinical nurse specialists, and ICU fellows) [15].

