### Outcomes

The clinical outcomes will be derived from data extracted from the patients’ EHRs related to inpatient hospital stay and up to 30 days after discharge to capture readmission. Using these data, the outcomes will be calculated and expressed at either the unit or patient level, as described herein. To facilitate generalizability and comparisons with other outcomes, the following outcomes, which are commonly assessed in other interventions for clinical deterioration [2,5,16], will be evaluated to address aim 1:

Number of RRT activations in response to adverse events per unit per month (RRT/unit/month; unit level)Number of code events per unit per month (codes/unit/month; unit level)Number of ICU escalations per unit per month (ICU/unit/month; unit level)Mortality per unit per month (deaths/unit/month; unit level)Readmission rates (30-day rates) per unit per month (30-day readmissions/unit/month; unit level)Length of stay in acute inpatient setting (patient level nested in unit)

We will also explore the process outcomes informed by the SEIPS 2.0 model and the implementation outcomes described by Proctor et al [17] to assess the ways in which the model and workflow changed the work system and, subsequently, the work processes (aims 2 and 3). Where possible, these outcomes will be derived from the patients’ EHRs and a secure text messaging platform to minimize the required data reporting by clinicians. A focused chart review of a subsample of patients will also be conducted for data not extracted through the methods described previously. Examples of these processes include the following:

Completion of documentation in the EHR (unit/month; unit level)Number and type of staff engaged in the intervention workflow (patient level nested in unit)Actions taken by the team engaged in the intervention workflow (patient level nested in unit)Time elapsed between alert and completion of workflow procedures, including documentation (patient level nested in unit)

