### Analysis

#### Quantitative Analysis

The primary aim is to assess the impact of the physician-only and team interventions on the unit-level clinical outcomes compared with baseline data. The secondary aim is to explore how the intervention is implemented by describing the process outcomes that were developed and launched as part of the intervention-specific workflow. For these process outcomes, the differences between the physician-only and team interventions will be statistically evaluated because baseline data will not be available for these outcomes. Poisson regression will be applied for unit-level count outcomes to determine the differences among the three phases of the study (baseline, physician-only, and team), followed by pairwise comparison. A multilevel, mixed-effects model will be used for patient-level outcomes to include the covariate unit to account for nesting. The level of statistical significance will be set at *P*<.05.

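### Time from alert to completed workflow exists only for completed workflows, so comparing it between the physician-only and team stages is open to selection bias of undetermined direction

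*Protocol article*

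**What the plan says.** All references are to the protocol article.

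- **Outcome** (Outcomes): one of four example process outcomes is "Time elapsed between alert and completion of workflow procedures, including documentation (patient level nested in unit"). The list serves aims 2 and 3 and is described as exploratory. A separate item is "Completion of documentation in the EHR (unit/month; unit level").
- **Population** (Sample): patient-level analyses include "patients who cross the high-risk CDI threshold (CDI≥65) during their inpatient stay and will thus be eligible for the intervention". Membership depends on crossing the threshold, not on completing the workflow.
- **Comparison** (Quantitative Analysis): for process outcomes, "the differences between the physician-only and team interventions will be statistically evaluated because baseline data will not be available for these outcomes".
- **Model** (Quantitative Analysis): "A multilevel, mixed-effects model will be used for patient-level outcomes to include the covariate unit to account for nesting".
- **Workflow** (Intervention Description and Model Validation): after an alert, clinicians begin with a check: "they first assess the patient to judge whether the alert is clinically relevant and accurate". A team huddle follows, and then: "The last step involves documentation using an EHR-based documentation tool".
- **Change between stages** (Implementation Strategy): in stage 2, "either the physician or the nurse on the team can initiate the downstream workflow"; in stage 1 only the physician can.

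**The concern.** The outcome and its population do not match. An elapsed time needs an end point, and a patient whose workflow stops early, is never documented, or is overtaken by a rapid response team (RRT) call, ICU transfer, death or discharge has none. A mixed-effects model of elapsed time, in its ordinary form, can use only patients who have a value.

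Completion is itself something that happens after the alert, and adding a second role that can start the workflow may change it. If the team stage completes workflows that the physician-only stage would have left undone, the completers in the two stages are different kinds of patients. The difference in their times then mixes two things: how fast comparable alerts are handled, and which alerts are handled at all.

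At stake is the reading of one timing measure for the stage 1 versus stage 2 comparison. The article wants to use process measures to help explain the clinical result, so a timing contrast of uncertain meaning would weaken that explanation.

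**Working it through.** **1. The plan's own figures.** The article states no completion share, completion time or power for this outcome. Its only computed figures concern RRT rates. Scenario 1 has 4.5 × 60 = 270 expected events at baseline and 4.5 × 0.75 × 41 = 138.4 in the team stage. Power is Φ(|ln 0.75| / √(1/270 + 1/138.4) − 1.96) = Φ(0.79) = 0.786, against about 80% stated. That agrees, and it has no bearing on this point.

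**2. The passages side by side.** Population: all who cross the threshold (Sample). Outcome: defined only if the last step, documentation, is reached (Outcomes; Intervention Description and Model Validation). Model: mixed-effects with unit (Quantitative Analysis). The article mentions no censoring, competing event or rule for unfinished workflows. Listing documentation completion as an outcome in its own right treats it as something to be measured, not taken for granted.

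**3. Size under assumed values.** Every input in steps 3 to 5 is an assumption. Stage 1 completes a share p₁ = 0.30 of alerts with mean 1 h. The team stage completes the same 30% with mean 1 h, plus extra alerts with mean m, for a total share p₂. Times are exponential, and 6 h is only an illustrative window.

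Mean among completers, team stage = [p₁ × 1 + (p₂ − p₁) × m] / p₂

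Share of all alerts completed by 6 h, team stage = p₁(1 − e⁻⁶) + (p₂ − p₁)(1 − e^(−6/m))

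In stage 1 these are 1.0 h and 0.30 × 0.9975 = 30%. With m = 3 h:

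| p₂ | Mean among completers | All alerts completed by 6 h |
|---|---|---|
| 0.40 | (0.30 + 0.10×3)/0.40 = 1.5 h | 39% |
| 0.50 | (0.30 + 0.20×3)/0.50 = 1.8 h | 47% |
| 0.60 | (0.30 + 0.30×3)/0.60 = 2.0 h | 56% |

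No alert is handled later in the team stage, yet the completers' mean rises by up to 100%.

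**4. The direction depends on the extra workflows.** With p₂ = 0.60:

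- m = 1 h: (0.30 + 0.30)/0.60 = 1.0 h. No bias.
- m = 0.7 h: (0.30 + 0.21)/0.60 = 0.85 h. The team looks faster although no alert is handled sooner among those both stages complete.
- Team truly 20% faster on the shared alerts, m = 3 h: (0.30×0.8 + 0.30×3)/0.60 = 1.9 h. A real gain is reversed.
- Team truly 20% faster on the shared alerts, m = 0.7 h: (0.24 + 0.21)/0.60 = 0.75 h, a ratio of 0.75 against a true 0.80. The gain is exaggerated.

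**5. A second mechanism.** Let latent times be lognormal (stage 1 median 20 h, log-SD 1.5), with completion seen only within 12 h, and let the team be uniformly faster with a true time ratio of 0.70. Simulation gives completion of 37% versus 46% and completers' means of 5.51 versus 5.13 h. The apparent ratio is 5.13/5.51 = 0.93, so the benefit shrinks but does not reverse.

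**The case against.** The strongest reply is that the article never says that patients without completion are dropped. It sets the population as all who cross the threshold, and a multilevel mixed-effects model does not strictly rule out a survival model with a random unit effect. Handling of censoring is the kind of detail a fuller plan may hold. This stands as a limit: the completer-only analysis is the natural reading of the text, not a stated rule. The point survives because the article itself fixes the outcome, population, comparison and model class, and in their ordinary reading these produce the mismatch.

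Second, documentation completion is already an outcome, and the Chart Review section samples 10% of charts from all patients with a triggered alert. Both would help a reader notice a change in completion. Neither repairs a patient-level comparison of times.

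Third, the workflow text does not say that an alert judged irrelevant ends undocumented. That branch may be in Figure 1, which is not shown. It is only one possible route to non-completion.

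Stronger inferences that the documents do not support:

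- **That the team stage will look slower.** This needs the added workflows to be materially slower than those already completed, and nothing in the article says so. Nor does it say that the team stage completes more.
- **That a mediation analysis is corrupted.** No statistical mediation model using this time is described. Aim 3 draws on interviews, configuration maps and a mixed methods matrix.
- **That this is the key measure of adding nurses.** It is one of four examples, beside staff engaged and actions taken.

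**Conclusion.** The point holds in limited form. The outcome exists only for completed workflows, the population is everyone who crosses the threshold, and completion may differ between the stages being compared. A comparison of times among completers is therefore open to selection bias.

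Its size cannot be determined from the article. Under the assumed mixture, with a stage 1 mean of 1.0 h, the team-stage mean among completers ranges from 0.85 to 2.0 h although the shared alerts are handled equally fast. A reader might infer from the upper end that the plan is biased against the team stage, but the same calculation gives no bias or a bias in its favour when the added workflows are as quick or quicker. The conclusion rests on two assumptions: that some alerts do not reach a documented workflow, and that patients without a value are left out of the model.

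The outcome is exploratory. The primary comparison of unit-level clinical outcomes does not use it and is unaffected. The matter should be settled before analysis, but it does not threaten the main result.

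**What to change.** Define the analysis on every alerted patient, starting at the first alert, in one of two ways:

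- **Time to completion**, with incomplete workflows censored at a prespecified horizon, and RRT activation, ICU transfer, death or discharge before completion treated as competing events. Report cumulative incidence of completion by stage.
- **Proportion completed within a prespecified window**, with all alerted patients in the denominator. The study team should choose and justify the window. The 6 hours in Intervention Description and Model Validation is lead time before a deterioration event and does not set a deadline for the workflow.

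Keep stage and unit in the model either way, and report the proportion of alerts completed by stage beside any time result. If times among completers are also shown, label them as descriptive.

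The cost is a change of wording and slightly more analysis. Alert and completion time stamps must be captured. The listed outcome already requires them, but EHR Data Extraction says that tools for discrete data capture still have to be developed, so those tools should record the alert time for every alerted patient. Dates and times of the competing events are also needed.

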### Data Collection and Procedures

Quantitative and qualitative data collection will be aligned to the SEIPS 2.0 framework. Mapping data to the framework aims to identify where multiple methods and sources of data can be used to explore each concept [14].

#### EHR Data Extraction

Quantitative data for processes and clinical outcomes will be extracted from the patients’ EHRs (Epic Systems Corporation) and the records of the clinical teams’ secure text messaging service (Voalte). Data extracted at the patient level will include notes, flowsheets of orders and referrals, and laboratory results, along with associated time stamps to assess the processes of the clinical teams’ response to clinical deterioration. Collecting these outcomes will require the development of electronic tools that will permit the capture and storage of these data discretely in the EHR as opposed to encounter-note text, for example.

#### Chart Review

Nondiscrete exploratory outcomes captured in the encounter notes will be investigated through chart review. To further explore the clinical processes related to the interruptive alert and clinical workflow, 10% of the patient charts will be reviewed to describe the workflow within the EHR after an alert has been triggered. The charts will be identified from a list of all patients for whom a high-risk alert was triggered during the evaluation period and stratified by unit to explore the potential between-units variation. Data elements and a template for the chart review will be determined based on the outlined SEIPS 2.0 constructs and will capture the events and orders documented in the EHR related to the CDI trigger, the location of documentation within the EHR, the role of the documenter, and interactions between the clinical team members. The chart review will follow the guidance described by Vassar and Holzmann [18].

#### Qualitative Interviews

Interviews with the clinicians will be conducted before and after the model and workflow are deployed to determine if and how the work system has changed (aims 2 and 3). The topic guide will be aligned with the concepts in the SEIPS 2.0 framework and the implementation outcomes [13,17]. The interviews are expected to take approximately 30-45 minutes and will be conducted by phone or video conference for the convenience of busy clinicians. The interviews will be recorded and transcribed for analysis. In addition, the outputs from the process improvement methods for designing the nursing workflow (process maps and pain point analysis) will be included as documentary data as part of the qualitative data set.

### Analysis

#### Quantitative Analysis

The primary aim is to assess the impact of the physician-only and team interventions on the unit-level clinical outcomes compared with baseline data. The secondary aim is to explore how the intervention is implemented by describing the process outcomes that were developed and launched as part of the intervention-specific workflow. For these process outcomes, the differences between the physician-only and team interventions will be statistically evaluated because baseline data will not be available for these outcomes. Poisson regression will be applied for unit-level count outcomes to determine the differences among the three phases of the study (baseline, physician-only, and team), followed by pairwise comparison. A multilevel, mixed-effects model will be used for patient-level outcomes to include the covariate unit to account for nesting. The level of statistical significance will be set at *P*<.05.

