### Setting

The intervention will be implemented in 6 primary general medicine adjustable acuity units at a quaternary academic hospital in the United States. The hospital has 605 beds, and most general medicine patients are cared for in 6 primary general medicine units. Each unit is served by physician teams, each with an average census of 12 and a maximum census of 20. The physicians spend most of their day rounding in many units and access the EHR through mobile devices, whereas the nurses spend most of their day in 1 unit working on a mobile desktop computer. These work setting characteristics were a key consideration in the intervention, implementation strategy, and study design.

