#### Power Calculation

On the basis of the aforementioned study design, we assessed the minimum effect size of the team intervention that can be detected with sufficient power (>80%). The percentage reduction in the number of RRT activations in response to adverse events per unit per month (RRT/unit/month) was chosen as the effect size measure because it is the most proximal of the clinical outcomes to the implemented workflow. As shown in Figure 2, our design provides a baseline period of 60 unit months and a team intervention period of 41 unit months. Assuming that the occurrence of RRT events follows a Poisson process, we conducted simulation studies with 10,000 replications to estimate the power curves using the following three scenarios. The first scenario assumes a mean rate of 4.5 RRT/unit/month during the baseline period for all 6 units. The second and third scenarios assume the following heterogeneous mean rates across the 6 units: 3.5 RRT/unit/month for 2 units, 4.5 RRT/unit/month for 2 units, and 5.5 RRT/unit/month for 2 units. In scenario 2, we assume that the team intervention is introduced to the units with lower rates at baseline first and the higher-rate units last, whereas in scenario 3, we assume the opposite. All scenarios use a two-sided α set at .05. Figure 3 shows the power curves for each scenario: scenarios 1, 2, and 3 indicate 80% power to detect a reduction in the RRT event rate of approximately 25%, 18%, and 30%, respectively.

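### Unit-month counts are analysed and powered as exactly Poisson with no stated allowance for overdispersion, so the 25% detectable reduction holds only if dispersion is 1

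*Protocol article*

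**What the plan says.** Under Quantitative Analysis the protocol article fixes the method for the primary aim: "Poisson regression will be applied for unit-level count outcomes to determine the differences among the three phases of the study". Pairwise comparisons follow, at P<.05. The next sentence gives a multilevel model with unit as a covariate, but only for patient-level outcomes. For the unit-level counts it states no unit term, dispersion parameter or robust variance.

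Power Calculation uses the same variance assumption and says so: "Assuming that the occurrence of RRT events follows a Poisson process". The comparison behind the power figure is described as follows: "our design provides a baseline period of 60 unit months and a team intervention period of 41 unit months". On rates, "The first scenario assumes a mean rate of 4.5 RRT/unit/month during the baseline period for all 6 units". Scenarios 2 and 3 let the rate differ between units but hold it constant within each unit during baseline. The result reported for scenario 1 is 80% power at a reduction of about 25%.

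Outcomes defines the RRT measure as a number of activations per unit per month. It is not a number of patients with an activation, and it is not expressed per admission or per patient-day.

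**The concern.** Poisson regression fixes the variance of each unit-month count at its mean. Two features of the RRT outcome make a larger variance plausible.

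- **Repeat events.** Activations are counted, so a patient who deteriorates more than once adds several correlated events to the same count.
- **No denominator.** Changes in unit volume or acuity from month to month go directly into the count, and no exposure offset is stated.

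Neither is removed by a unit term, which absorbs only stable differences between units. If residual variance exceeds the mean, the model's standard errors are too small. False positives then exceed 5% in the phase comparisons, and a test that keeps its level has less power than stated. What is at stake is the error rate of the primary-aim analysis of RRT and the detectable effect published for it.

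**Working it through.** **Inputs from Power Calculation.** Baseline 60 and team 41 unit-months; 4.5 RRT per unit-month (scenario 1); alpha .05 two-sided; target power 80%; stated detectable reduction about 25%.

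**Assumed input.** Dispersion phi = variance/mean of a unit-month count. The document gives none, so a range is shown. Unit-months are taken as independent.

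**Step 1: reproduce the stated figure (phi = 1).**

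- Expected baseline events: 60 × 4.5 = 270.
- Expected team-phase events at a 25% reduction: 41 × 4.5 × 0.75 = 138.4.
- SE of the log rate ratio: √(1/270 + 1/138.4) = 0.1045.
- Power: Φ(|ln 0.75|/0.1045 − 1.96) = Φ(2.752 − 1.96) = Φ(0.792) = 78.6%.
- Solving for 80% power gives a 25.4% reduction. Simulation with 10,000 replications gives 79–80% power at 25%.

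The stated figure of about 25% is therefore right on its own inputs.

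**Step 2: let phi exceed 1.**

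- Type I error of the plain Poisson test: 2 × [1 − Φ(1.96/√phi)].
- Power of a dispersion-scaled test at a 25% reduction: Φ(2.752/√phi − 1.96).
- Detectable reduction r: solve |ln(1 − r)| = (1.96 + 0.842) × √phi × √(1/270 + 1/(184.5 × (1 − r))), where 184.5 = 41 × 4.5.

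| phi (assumed) | Type I error, plain Poisson | Valid power at 25% | Detectable reduction, 80% power |
|---|---|---|---|
| 1.0 | 5.0% | 78.6% | 25.4% |
| 1.2 | 7.4% | 71.0% | 27.7% |
| 1.5 | 11.0% | 61.3% | 30.8% |
| 2.0 | 16.6% | 49.4% | 35.3% |

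Worked line for phi = 1.5: 1.96/1.225 = 1.600, so type I error is 11.0%; 2.752/1.225 − 1.96 = 0.287, so power is 61.3%.

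**Step 3: check by simulation.** Negative binomial unit-month counts (5,000 replications) gave plain Poisson type I error of 7.0%, 11.0% and 16.8% at phi 1.2, 1.5 and 2.0. The scaled test held 4.9–5.1%, with power at 25% of 70.0%, 61.1% and 48.9%.

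**Step 4: how much rate variation these values imply.** If the extra variance comes only from a rate that varies between unit-months, phi = 1 + mean × CV². At a mean of 4.5, phi of 1.2, 1.5 and 2.0 needs a CV of √(0.2/4.5) = 21%, √(0.5/4.5) = 33% and √(1/4.5) = 47%. The same formula shows why the table does not transfer to rarer outcomes: at an assumed 0.5 events per unit-month, a 47% CV gives phi of only 1 + 0.5 × 0.222 = 1.11.

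**Step 5: what scaling does not repair.** With month effects shared by all units, at an assumed CV of 20%, simulated type I error was 15.8% for plain Poisson and still 12.5% after scaling.

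**The case against.** The strongest objection is that the article openly labels the Poisson process as an assumption, its 25% is correct under that assumption, and no dispersion value is given. A condensed article may also leave variance estimation and dispersion checks to an analysis plan that is not shown. This stands in part. It rules out saying that the P values are too small or that the power is not achieved; both are conditional. It does not remove the point, because the article names a specific model for the primary-aim counts and publishes a detectable effect that depends on dispersion being exactly 1.

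A reader might infer that the article's own unit rates, "3.5 RRT/unit/month for 2 units, 4.5 RRT/unit/month for 2 units, and 5.5 RRT/unit/month for 2 units", already prove overdispersion, since pooling them gives a variance ratio of 1 + 0.667/4.5 = 1.15. They do not. With fixed unit rates each phase total is a sum of Poisson counts and is itself Poisson. In simulation with equal team months per unit and no unit term, type I error was 4.96%. It rose to about 6–10% only when team months were unequal across units (six assumed roll-out patterns). That is confounding of phase with unit, which a unit term removes and a dispersion parameter does not.

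A reader might also turn to the census figures under Setting. They describe physician teams' caseloads, not the monthly volume of a unit.

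Finally, the larger dispersion values are illustrative. The between-unit CV in the article's scenarios is √0.667/4.5 = 18%, below the 21% that rate variation alone would need for phi of 1.2. Repeat activations could add to this, but no frequency is given.

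**Conclusion.** The point holds in conditional form. The unit-level counts for the primary aim are analysed and powered under Poisson variance with no stated allowance for extra variation, although RRT activations can repeat within a patient and carry no volume denominator. The 25% figure is correct if dispersion is 1 and optimistic if it is above 1. Across an assumed range of 1.2 to 2.0, type I error of the stated test is about 7–17%, valid power at a 25% reduction is about 71–49%, and the detectable reduction is about 28–35%.

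These sizes rest on independent unit-months, 4.5 RRT per unit-month and the 60 versus 41 comparison. They should not be carried over to rarer outcomes; deaths, in addition, cannot repeat within a patient. The document does not show that dispersion exceeds 1. What it supports is that a dispersion-robust model is a better stated choice at little cost.

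**What to change.** - **Quantitative Analysis:** fit the unit-level counts as negative binomial, or as quasi-Poisson with Pearson-scaled standard errors and a t reference, with unit in the model.
- **Power Calculation:** estimate dispersion within units from the 60 baseline unit-months (six units by ten months), so that stable unit differences are not counted as dispersion. Restate the detectable reduction at that value or over a range such as 1.0 to 2.0.
- **Shared month effects:** state that scaling does not cover variation common to all units in a month. Either handle it separately or name it as a limitation.

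The cost is a change of analysis wording and one rerun of the power simulation, with no new data. The downside is a somewhat less favourable stated detectable effect if the estimated dispersion exceeds 1.
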